#### Laboratory data

Blood investigations are performed at the accredited on-site laboratory or central laboratory at Singapore General Hospital. They include:
Glycaemic control: HbA1c (onsite using the DCA® Vantage Analyser).Lipid panel (total cholesterol, HDL-cholesterol, triglycerides and calculated LDL-cholesterol) at central laboratory with the Roche® Cobas c702 machine using the enzymatic colourimetric method.Renal panel (serum electrolytes and creatinine levels) using the Roche® Cobas c702 machine in the central laboratory. The eGFR is computed using the Chronic Kidney Disease Epidemiology Collaboration (CKD-EPI) equation [18].Urine albumin and urine creatinine using the Beckman DXC700AU machine in the central laboratory.

#### T2DM related literacy and behaviour profiles using self-rated scales

European Quality of Life-5 dimensions (EQ-5D-5L) scale. It is a brief, generic health-status instrument validated in the local Asian population [19]. The first part of the scale contains 5-point Likert-type items (no/slight/moderate/severe/extreme) to assess the five dimensions of a person’s health status (mobility, self-care, usual activities, pain/discomfort and anxiety/depression). The second part is the EQ-Visual Analog Scale (EQ-VAS), which is a vertical, 0 (the worst health state) to 100 (the best health state) hash-marked numerical scale for self-rating of overall health.Medication adherence is assessed using the Medication Adherence Report Scale (MARS-5) for oral hypoglycaemia agent. The MARS-5 comprises five items which describe a range of non-adherent behaviours, phrased in a non-threatening and non-judgmental way to normalise non-adherence. The scale allows the patients to rate their adherence over five points, rather than on the basis of a “yes/no” or “high/low” dichotomous response, thus providing more detail and differentiation between individuals [20].Medication Possession Ratio (MPR) for insulin. The MPR is a ratio of the total days’ supply of insulin to the number of days of study participation per participant [21].Michigan Diabetes Knowledge Test (MDKT). The MDKT consists of a 14-item general test and a 9-item insulin use subscale to assess literacy on T2DM and treatment [22].Self-care inventory (SCI): Self-care is defined as the daily regimen tasks that a patient performs to manage T2DM. SCI is a self-reported questionnaire to assess patients’ perceptions of self-care behaviours, especially on their adherence to their treatment prescriptions, regardless of their treatment regimens [23].International physical activity questionnaire - short form (IPAQ-SF). The IPAQ-SF records physical activity at four intensity levels: (1) vigorous-intensity activity such as aerobics, (2) moderate-intensity activity such as leisure cycling, (3) walking and (4) sitting [24].Diabetes-related distress using the Problem Area in Diabetes (PAID) scale. It is a 20-item scale to measure emotional distress in people with diabetes mellitus and has been validated in a Singaporean population [25, 26].

### Outcomes

#### Primary outcome measures

The primary outcome will be the mean HbA1c and magnitude of its change on enrolment and at 6 months in patients in the intervention arm compared with those in the control arm.

#### Secondary outcomes at stipulated time points

Post-intervention HbA1c at 12 and 24 months.On-site systolic and diastolic blood pressure readings.Weight and BMI.Absolute and change in scores in EQ. 5D-5L, MARS-5, MPR, MDKT, SCI, IPAQ-SF, PAID.Healthcare utilisation based on hospitalisation and polyclinic treatment bills.Incidence of macro and microvascular complications, such as coronary, cerebral, renal retinal and peripheral vascular diseases diagnosed by clinicians and documented in the EMR. Renal outcomes will be determined from the serum creatinine, urine albuminuria and eGFR.Fidelity of patients to the stipulated telemonitoring protocol. It will be computed based on the proportion of them adhering to or exceeding the recommended frequency of self-monitoring of the three key clinical parameters (systolic and diastolic blood pressure, weight and capillary blood glucose) and the proportion of them who have viewed all the health education videos. These data will be retrieved directly from the OPTIMUM system.

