The overarching aim of this mixed-method study is to assess the effectiveness of the OPTIMUM telemonitoring system in improving diabetic management of patients with T2DM by supporting and enhancing their self-management. It includes a randomised control trial (RCT) to compare the glycaemic control, based on the magnitude of HbA1c change at recruitment and at 6th-month post-enrolment, among patients with T2DM in the intervention arm with those in the control arm. The secondary aims include a comparison of blood pressure and weight control; quality of life, medication-adherence, confidence in self-management, diabetic literacy and related distress and healthcare utilisation using validated questionnaires; and incidences of emerging retinal, renal, coronary and cerebrovascular complications of the patients in the two arms at stipulated time-points over 24 months. The study also aims to understand the patients’ experience, acceptance and perceived usefulness of the OPTIMUM system in the intervention arm using qualitative research methods.

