### OPTIMUM telemonitoring system

The OPTIMUM system rides on the cloud-based Philips® *VitalHealth* platform for population health management. The platform is currently being used in more than 100 healthcare networks in countries in North America and Europe and will be launched in Singapore in this study. The study team has leveraged on an innovative strategic approach based on Philips® *Co-Create* methodology to culturally adapt the platform to the local Asian population. The *Co-Create* methodology is a step-wise, iterative, people-centric and multi-disciplinary approach to creative innovation and problem-solving. Based on a mindset of collaboration, it extracts thoughts, intentions, and creative ideas via a facilitated workshop. During the workshop, stakeholders, including the researchers, clinicians, nurses, clinic administrators and patients deliberate with the technical team to develop and culturally adapt both the patient-facing smartphone OPTIMUM app and clinician-facing web-app. Two collaborative interviews were conducted through an iterative process to develop and refine the solution.

The OPTIMUM system was developed after iterative solution refinements and two rounds of user acceptance testing. Both the patient OPTIMUM app and clinician web-portal leverage on the Amazon Web Services (AWS)-hosted cloud solution. The cloud-based, containerised microservice architecture makes it a highly accessible and easily scalable health management solution. It also supports role-based authorisation to allow different clinician roles and for them to have access only to specific patient data set to ensure privacy. It is brand- and system-agnostic to various monitoring devices available in the community.

The OPTIMUM system allows for remote patient monitoring, raises their health and diabetes literacy via locally produced patient education videos, and timely interventions via phone call by the clinicians and nurses in the study team when the patients’ clinical parameters exceed pre-determined thresholds. These thresholds are set by the investigators based on local clinical practice guidelines [17] and are embedded in the OPTIMUM management algorithm. The OPTIMUM system facilitates daily monitoring of patients’ parameters and generates tasks based on pre-defined criteria embedded in the OPTIMUM protocol (Additional file 2). The nurses will also take actions according to the protocol algorithm.

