#### Tele-monitoring and tele-support

Patients will self-monitor their body weight, blood pressure, heart rate and capillary glucose levels using the devices according to the stipulated schedule in the OPTIMUM system. The readings will be automatically transmitted through the OPTIMUM system to the clinical care team who will review them asynchronously using the clinician-facing dashboard. Personal target thresholds are pre-set based on clinical practice guidelines (Additional file 2). The study team nurses will phone the patients based on the OPTIMUM treatment algorithm to assess, advise and manage patients accordingly based on their clinical parameters.

Patients will receive immediate feedback via push notifications from the app if their clinical parameters deviate beyond the stipulated range. They will be prompted to respond to questions in the messages to verify their measurements, screen for any related symptoms and assess adherence to medications. The nurses will review their responses before deciding on the appropriate actions based on the pre-specified escalation protocols. The actions include telephone consultations or arranging for patients to return to the polyclinic for assessment in consultation with the clinicians. Patients will also be encouraged to contact the nurses should they have queries about their chronic conditions.

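### The bills-based utilisation outcome has no component for the study-team tele-contacts that only the intervention arm receives, and its data source is stated in two ways

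*Protocol article*

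**What the plan says.** **Definition.** The list under Secondary outcomes at stipulated time points gives "Healthcare utilisation based on hospitalisation and polyclinic treatment bills". It names no other source for this outcome.

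**Competing source.** The aims at the end of the Background compare the arms on "diabetic literacy and related distress and healthcare utilisation using validated questionnaires", and the abstract does the same. The section on self-rated scales describes EQ-5D-5L, MARS-5, MPR, MDKT, SCI, IPAQ-SF and PAID. None of these measures use of health services, and the Table 1 footnotes name no such instrument.

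**Contacts in the intervention arm.** The OPTIMUM telemonitoring system section describes "timely interventions via phone call by the clinicians and nurses in the study team when the patients’ clinical parameters exceed pre-determined thresholds". The section on tele-monitoring and tele-support adds: "The study team nurses will phone the patients based on the OPTIMUM treatment algorithm to assess, advise and manage patients accordingly". On escalation it says: "The actions include telephone consultations or arranging for patients to return to the polyclinic for assessment in consultation with the clinicians". The abstract sets remote supervision at 6 months. Under Intervention, controls stay on standard care, and no study calls are described for them.

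**Use of system data.** The outcomes section draws on the OPTIMUM system only for patient fidelity, that is self-monitoring frequency and videos viewed. No outcome counts calls or tele-consultations.

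**The concern.** There are two separate problems.

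The first is documentary. One outcome has two stated sources, and only one of them, bills, is backed by anything else in the article.

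The second is differential measurement. Care obtained outside the polyclinic and hospitals would be missed in both arms alike. Study-team tele-contacts exist in one arm only. If they produce no bill, a problem handled by phone in the intervention arm contributes nothing to the outcome, while the same problem handled at a clinic visit in the control arm is counted. Randomisation does not remove a difference in what is measured.

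What is at stake is interpretation. The article says the results should inform policy makers on adopting telemedicine, and it describes current care as often resource intensive. A lower bills figure could then be read as less use of care overall, although the staff contact that the programme itself requires had not been counted.

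**Working it through.** **Figures available.** The article gives no figure for utilisation. Its only power figure, for HbA1c, reproduces:
- Mean variance = (1.4² + 1.3²)/2 = 1.825, so SD = 1.351.
- With a difference of 0.5, two-sided 5% and 80% power, n = 115 per arm by the normal approximation.
- 115/(1 − 0.30) = 164.3, hence 165 per arm and 330 in total.

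Nothing in this point depends on those numbers.

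**What the measure includes.** Per patient, let B_I and B_C be billed polyclinic and hospital contacts in the intervention and control arms, and T the unbilled tele-contacts in the intervention arm.
- Difference measured from bills: B_I − B_C.
- Difference in all provider contact: (B_I + T) − B_C.
- Gap between the two: T, which is zero or more and arises in the intervention arm only.

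If utilisation is expressed as money, the gap is T times a unit cost, which the article does not give.

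**What the article fixes about each term.**

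| Term | What is stated | What is not stated |
|---|---|---|
| T | Calls and telephone consultations, triggered by the algorithm, over 6 months | Number of calls; whether any are billed (if all are, T = 0) |
| B_I | Standard care, plus returns to the polyclinic arranged on escalation | Whether any scheduled visit is dropped |
| B_C | Standard care, with a doctor's consultation every 3 to 6 months | Actual visit rate |

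The escalation sentence names two routes: "The actions include telephone consultations or arranging for patients to return to the polyclinic for assessment". A return visit is a polyclinic contact that bills would be expected to show. A telephone consultation may not be.

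**Why no size can be given.**
- T needs a call rate and a billing rule, and neither is stated.
- Scheduled visits number 6/6 = 1 to 6/3 = 2 over 6 months, and 24/6 = 4 to 24/3 = 8 over 24 months.
- Suppose, purely for illustration, that one visit were replaced by calls. That would be 1/2 to 1/1 (50–100%) of scheduled visits over 6 months, but 1/8 to 1/4 (12.5–25%) over 24 months. The article does not say that any visit is replaced, so neither range is an estimate.
- The supervised period covers 6/24 = 25% of follow-up. For the other 18 months no study tele-contact is described.

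**Direction.** If T is above zero, leaving it out always understates contact in the intervention arm. The sign of B_I − B_C is open: avoided visits would lower B_I, and returns prompted by monitoring would raise it.

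**The case against.** The strongest reply has four parts.

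1. **Billing is assumed.** No billing rule appears anywhere. The supervising staff are also described as primary care physicians and nurses, so the calls need not be pure research activity. This stands: omission of the calls is a plausible inference from delivery by the study team, not a documented fact, and the point must stay conditional.

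2. **Bills answer a coherent question.** They show what the programme does to use of existing polyclinic and hospital services. The programme's own calls are its delivery, and controls cannot receive them. This stands as a reason to keep the bills measure and not to replace it with a combined count. It does not justify reporting the result as healthcare utilisation without a qualifier.

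3. **The article is condensed.** How calls are logged and how utilisation is derived may be set out in the full protocol. That is fair for detail, but the article is not silent here: it names one source in the outcome list and another in the abstract and aims.

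4. **The questionnaire wording may be loose drafting.** It closes a long list and may be meant for the other items. That is likely, and it makes the correction easy. It has no bearing on whether tele-contacts are counted.

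A reader might go further and infer that calls replace clinic visits, so that the comparison must favour OPTIMUM. The article does not support this. OPTIMUM is presented as supporting standard care, no scheduled visit is said to be dropped, and escalation can add visits.

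**Conclusion.** The point holds in a limited form. The source of the utilisation outcome is stated inconsistently, and that rests on no assumption. The bills-based measure has no component for study-team tele-contacts, which are described for the intervention arm only, in the first 6 of 24 months. If those contacts are unbilled, provider contact is understated in that arm alone, and a bills-only result could be mistaken for lower overall utilisation.

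The size cannot be computed and the net direction of the bills comparison is not fixed. It would therefore be wrong to infer that the utilisation result is bound to be false, or to attach a percentage fall in visits or a number of uncounted calls to it. One secondary outcome is affected. The primary HbA1c comparison and the sample size are not.

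**What to change.** - Name bills as the single data source for utilisation, and remove the reference to validated questionnaires for this outcome from the abstract and the aims.
- Keep the bills-based comparison, labelled as use of polyclinic and hospital services.
- Beside it, report the number of OPTIMUM nurse and physician calls and tele-consultations from system or call records, and the combined total.
- State whether any of these contacts are billed, and count a billed call only once.
- Do not conclude lower overall utilisation from bills alone.

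**Cost.** A small data export and a few changes of wording. The system generates tasks from pre-defined criteria and already supplies the fidelity data, so part of the record should exist; calls that it does not log would have to come from call records. Any unit cost applied to calls would be an assumption and should be shown as one. The result may look less favourable to the intervention.

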### Adverse event reporting

Serious adverse event (SAE) resulting in death, hospitalisation or significant disability and incapacity in patients during the conduct of this study will be immediately reported to the institution review board and documented as SAE data in the eventual analysis of the data.

Adverse event (AE) can be any unfavourable and unintended sign (including an abnormal laboratory finding) and symptoms reported by the patients during the study. AE may be reported directly by patients, via the OPTIMUM app or discovered by the nurses via phone calls. Such information will also be documented and computed for analysis. The Principal Investigator will report the SAE and AE to the Institutional Review Board (CIRB) within the stipulated timeframes.

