### Setting and participants

The trial will be conducted at a polyclinic located in Sengkang, an estate in north-eastern Singapore with a population of about 300,000 multi-ethnic Asian residents [12]. This polyclinic serves approximately 900 to 1000 patients daily during office hours in each weekday and is similar to the other polyclinics in Singapore [11]. Current standard of care of patients with T2DM at polyclinics include 3–6 monthly doctor’s consultation with HbA1c readings; fasting laboratory panel tests (electrolyte panel, lipid panel, liver panel and urine albumin-creatinine ratio) at diagnosis and then every 6 to 12 months; and annual diabetic retinal photograph and diabetic foot screening. Patients may be referred to dieticians for dietary advice, nurses for co-management or onwards to tertiary care specialists at the discretion of the attending physician.

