### Intervention

A set of three Bluetooth-enabled devices, a weighing scale (Xiaomi Body Composition Scale 2), a glucometer (Accu-chek Guide set, Model 929 mmol/L) and an electronic blood pressure monitor (Smartfuture Medcheck Blood Pressure Monitor SFB01), will be allocated to each patient in the intervention arm for their sole use during the trial. The CRCs or nurses in the study team will induct these patients to the use of the three devices, and synchronise them with the OPTIMUM app. The patients will use the app to provide their responses to the health assessment questionnaires, which will then automatically transmit the data to the nurses for review.

Patients randomised to the control arm will continue with standard care as described previously and may continue using their own devices, if any, for their own monitoring. Patients randomised to the intervention arm are expected to perform the following tasks in the first 6 months after recruitment (Fig. 2).

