#### Safety data analyses

The number and proportion of patients experiencing T2DM related complications will be tabulated for each arm with 95% confidence intervals using the exact method. The number and proportion of patients with AE and SAE will be tabulated and compared between both arms.

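### Non-serious adverse events are compared between arms although two of the three named reporting routes belong to the intervention, which tilts the comparison towards more events with telemonitoring

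*Protocol article*

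**What the plan says.** All references are to the protocol article.

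- **Routes.** Adverse event reporting states: "AE may be reported directly by patients, via the OPTIMUM app or discovered by the nurses via phone calls". It adds that this information will be documented and used in the analysis.
- **Definition.** The same section is broad: "Adverse event (AE) can be any unfavourable and unintended sign (including an abnormal laboratory finding) and symptoms reported by the patients during the study".
- **Comparison.** Safety data analyses states: "The number and proportion of patients with AE and SAE will be tabulated and compared between both arms". It does not restrict the source of the events and names no test for them.
- **Intervention arm.** Under Tele-monitoring and tele-support, "The study team nurses will phone the patients based on the OPTIMUM treatment algorithm to assess, advise and manage patients accordingly". When readings fall outside the set range, the app also contacts patients: "They will be prompted to respond to questions in the messages to verify their measurements, screen for any related symptoms and assess adherence to medications". Under Intervention, the patients' tasks are placed in the first 6 months after recruitment.
- **Control arm.** Under Intervention: "Patients randomised to the control arm will continue with standard care as described previously and may continue using their own devices, if any". Under Setting and participants: "Current standard of care of patients with T2DM at polyclinics include 3–6 monthly doctor’s consultation with HbA1c readings".
- **Shared elements.** Demographic and clinical data lists hypoglycaemia and hypotension among the data recorded by questionnaire, without limiting this to one arm. The Abstract has both arms assessed at baseline and at 6, 12 and 24 months.

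**The concern.** How often a mild event is recorded depends on how often someone measures, asks or listens. Intervention patients receive a glucometer and a blood pressure monitor, are prompted about symptoms after an abnormal reading, and are phoned by nurses. Control patients have their own report, their usual consultations and the study visits. With a definition that takes in any unfavourable sign or symptom, the same low glucose or low pressure can become a recorded AE in one arm and pass unrecorded in the other.

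If all recorded events enter one comparison, equal true risks look like an excess with telemonitoring. Conversely, a real excess could be dismissed as a product of closer surveillance. Without the source of each event, the data could not separate the two. The Discussion intends the results to inform policy makers, and the steering committee reviews AE data every six months.

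**Working it through.** **Inputs from the documents.** The Sample size calculation section gives 165 per arm. This reproduces: n = (1.96 + 0.8416)² × (1.4² + 1.3²) / 0.5² = 7.849 × 3.65 / 0.25 = 114.6, so 115; 115 / 0.70 = 164.3, so 165. The significance level is 5%. App tasks last 6 months and follow-up 24 months.

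**Assumptions.** The documents give no AE risk or capture rate. I take a true risk p of 20% or 30%, equal in both arms; capture of 90% in the intervention arm and s = 50% or 70% in control; and Fisher's exact test, two-sided. The Statistical analysis section names Fisher's test directly after cerebrovascular events, so its use for AEs is assumed. Rejection probabilities come from exact enumeration of two binomials with 165 per arm.

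**Case A: the asymmetry spans the whole comparison period.** Observed risk = p × capture. Here p is the risk within that period.

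**Case B: 90% capture for 6 of 24 months, control-level capture afterwards, constant event rate.** Mean intervention capture w = (6 × 0.9 + 18 × s) / 24, which is 0.60 for s = 0.5 and 0.75 for s = 0.7. Observed risk is 1 − (1 − p)^w in the intervention arm and 1 − (1 − p)^s in control. For p = 0.30 and s = 0.5: 1 − 0.7^0.60 = 19.3% against 1 − 0.7^0.50 = 16.3%.

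| True risk | Control capture | A: observed | A: significant | B: observed | B: significant |
|---|---|---|---|---|---|
| 30% | 50% | 27% vs 15% | 73% | 19.3% vs 16.3% | 8.4% |
| 30% | 70% | 27% vs 21% | 21% | 23.5% vs 22.1% | 4.6% |
| 20% | 50% | 18% vs 10% | 50% | 12.5% vs 10.6% | 6.1% |
| 20% | 70% | 18% vs 14% | 13% | 15.4% vs 14.5% | 4.1% |

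With equal capture, Fisher's test rejects in about 3–4% of trials, because it is conservative. The apparent risk ratio is 1.29 (0.9 / 0.7) to 1.80 (0.9 / 0.5) in case A and about 1.06 to 1.19 in case B.

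**Sensitivity, under case A.**
- With 115 per arm, the number left after 30% dropout, the four figures fall to 56%, 15%, 35% and 10%.
- With capture of 90% against 80%, the risk ratio is 0.9 / 0.8 = 1.12 (rounded down), and a significant false excess on the intervention appears in 5.3% of trials at true risk 20% and 9.7% at 40%.

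**The case against.** The strongest case on the other side has four parts.

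- **Shared routes exist.** Patients in either arm can report directly, and the questionnaire covers hypoglycaemia and hypotension, the events that devices would reveal most. Controls may also use their own devices. This stands and narrows the gap. It does not close it, because the planned comparison is not tied to those shared sources.
- **The extra capture is time-limited.** App tasks end at 6 months, while AEs are counted over the study. This stands and is why case B is so much milder. Two qualifications apply. Events concentrated early would be diluted less. A comparison made when all patients have completed month 6 would be close to case A, although the text does not state that the planned interim analysis includes the AE comparison.
- **Details of the AE tables may sit elsewhere.** Which source feeds which table is often left to an analysis plan. The article does, however, state both the routes and the between-arm comparison, and taken as written they do not match.
- **Restricting the sources does not equalise detection.** Patients who own a study glucometer will know of more low readings and may report them at visits. This stands and limits what the fix can achieve.

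A reader might also infer that controls have no AE route at all, that the entire safety comparison is uninterpretable, or that a false signal is likely. The text does not support these. Direct report is named as a route. SAEs (death, hospitalisation, significant disability) and clinician-diagnosed complications in the medical record depend little on the app or calls. The large percentages require strong asymmetry throughout the period compared.

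**Conclusion.** The point holds for non-serious AEs. Two of the three named routes belong to the intervention, and the planned comparison does not confine itself to sources common to both arms. The expected direction is towards more AEs in the intervention arm. It does not depend on the test, since an untested table would show the same tilt.

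The size cannot be derived from the documents. Under the assumptions above, a false difference appears in about 13–73% of trials if the asymmetry covers the whole period compared. It appears in about 4–8% over 24 months if it is confined to the first 6 months at a constant event rate, which is little above the 3–4% seen with equal capture. The HbA1c primary outcome and its sample size are untouched.

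**What to change.** 1. Add a field to the AE form for the source of each event, from the start of data collection, because it may not be recoverable later.
2. Base the main between-arm AE comparison on events collected the same way in both arms: AE questions put to both arms by questionnaire at the study visits, plus hospitalisation and medical records. The schedule table is not legible in the text available, so confirm that it places these questions at the same visits for both arms.
3. List events found only through the app, device readings or nurse calls separately and descriptively, for the intervention arm.
4. Keep an all-source table by arm, and leave all reporting to the review board unchanged.

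The cost is one form field and one changed safety table. Fewer AEs enter the comparison, and recall at visits is imperfect. Some asymmetry remains because device users know of more abnormal readings; the report should say so.
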